### Recruitment {15}

The project group collaborates closely with the psychiatric outpatient clinic at UNN-HF, Tromsø. Written information about the project is sent to participants on the waiting list. The project has been communicated to all general practitioner offices in Tromsø as well as the community centres for low-threshold services for mental health support. Additionally, information about the project is distributed through multiple channels such as the local media on the radio and in newspapers and internal media at the hospital and university; the project has a website and physical posters have been hung around the city of Tromsø.

## Assignment of interventions: allocation

### Sequence generation {16a}

The RCT will be run with an allocation ratio of 1:1 to the two groups (iTBS and sham). We expect a 1:1 ratio of males to females since the groups will be stratified by gender in the randomization.

### Concealment mechanism {16b}

The randomization will be performed in MATLAB (https://se.mathworks.com/products/MATLAB.html), with the “randperm” command that performs randomization in four permuted blocks to groups and gender in a single operation. The a priori randomization procedure in MATLAB will be performed by a research assistant prior to the start of the study. This research assistant is not involved in the data collection.

The research assistant will produce numbered coloured envelopes (e.g. pink = female, blue = male), each containing a number indicating the type of coil to be used (e.g. 1 = active, 2 = sham).

### Implementation {16c}

The staff member who performs the stimulation procedure will open the envelope. The staff members who provide iTBS will not assess the patient. Clinicians who assess the patients will not be aware of the treatment group. Thus, neither the clinician who assesses the patient nor the patient will know which treatment is provided. A study identification code will be allocated to each participant upon entry. Their name or national identity number will not appear in the research data collected.

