### Trial design {8}

This trial is a single-centre, randomized, sham-controlled, parallel-group, double-blind clinical trial. Participants will be recruited prospectively.

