## Interventions

### Explanation for the choice of comparators {6b}

In this RCT, the effects of iTBS will be compared against sham iTBS. Sham iTBS resembles the active iTBS condition and provides a sensory experience that is difficult to separate from real iTBS for naïve participants. The use of a placebo treatment will allow us to separate the effect of iTBS from other non-iTBS-specific factors.

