### Intervention description {11a}

Theta burst stimulation will be performed with a Mag & More PowerMag EEG 100 system (https://magandmore.com) with a double PMD70 p-cool figure-of-eight coil. Sham stimulation will be performed by the double PMD70 p-cool figure-of-eight coil Sham system. The sham system has an identical look, weight and sound compared to the active coil, and delivers electrical stimulation that can be felt at the skin but without penetrating the skull. Resting-motor threshold (RMT) will be determined prior to stimulation in accordance with the consensus guidelines for rTMS [21]. ITBS will be delivered with the same parameters as in Blumberger et al., [8]: 120% RMT triplet 50 Hz bursts repeated at 5 Hz; 2 s on and 8 s off, 600 pulses per session with a total duration of 3 min 9 s. Treatment will be provided for 10 days for two consecutive weeks (except Saturdays and Sundays). Before the first treatment, participants will perform MRI examinations (T1, DTI, fMRI) and the high-resolution T1-weighted obtained at that point will be used for real-time MRI-guided neuro-navigation for optimal coil positioning. A Localite TMS-navigator system (https://www.localite.de) will be used for the determination of the target area within the DLPFC. The Localite system visualizes the patient’s brain on a pc-screen based on the T1 images, and the coil is connected to the Localite system making it possible to move the coil over the desired brain structure and correctly position it. The target MNI coordinate will be *x* − 38, *y* + 44, *z* + 26, based on the findings of Fox et al. [12] who identified this point based on clinical outcomes and whole-brain functional connectivity for rTMS studies.

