### Criteria for discontinuing or modifying allocated interventions {11b}

The criteria for discontinuing or modifying allocated interventions for a given participant include the following: worsening of disease, report of adverse side effects, withdrawal of consent, change in drugs or not receiving stimulation on more than 2 days. If the patient is absent from one or two stimulations, these will be added to the treatment schedule. For safety reasons, participants will be asked about sleep, alcohol, illegal drugs and medication use prior to each simulation. Participants will be asked about their well-being prior to and after each iTBS stimulation. The participants will be asked to drink no more than one unit of alcohol the night before stimulation. If the patient reports drinking more alcohol, stimulation will be postponed to the day after. Stimulation will also be postponed if the participant reports significant tiredness and/or lack of sleep the night before [23].

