## Assignment of interventions: blinding

### Who will be blinded {17a}

The patient will be blinded. The assessor of the patients’ clinical symptoms will be blinded. The staff members who provide iTBS will not assess the patient. Clinicians who assess the patients will not be aware of the treatment group. Thus, neither the clinician who assesses the patient nor the patient will know which treatment is provided. Four weeks after the last stimulation day, treatment allocation will be disclosed to the patient.

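### Stimulating staff open an envelope showing the coil type, and only the patient and clinical assessor are blinded, which leaves a performance-bias route to BDI-II and MADRS

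*Protocol article*

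**What the plan says.** Concealment mechanism {16b} has a research assistant, who takes no part in data collection, prepare numbered coloured envelopes, "each containing a number indicating the type of coil to be used (e.g. 1 = active, 2 = sham". Implementation {16c} then says who uses them: "The staff member who performs the stimulation procedure will open the envelope".

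Who will be blinded {17a} names the patient and the assessor of clinical symptoms, and concludes: "Thus, neither the clinician who assesses the patient nor the patient will know which treatment is provided". The operator is not on the list. The safeguard offered for operators is separation of roles: "The staff members who provide iTBS will not assess the patient". Trial design {8} gives the label: "This trial is a single-centre, randomized, sham-controlled, parallel-group, double-blind clinical trial".

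On the equipment, Intervention description {11a} says: "The sham system has an identical look, weight and sound compared to the active coil". It adds that the sham delivers electrical stimulation felt at the skin without penetrating the skull. Explanation for the choice of comparators {6b} says the sham "provides a sensory experience that is difficult to separate from real iTBS for naïve participants".

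Treatment runs for ten days over two weeks. On contact around each session, Criteria for discontinuing or modifying allocated interventions {11b} says: "Participants will be asked about their well-being prior to and after each iTBS stimulation". It does not say who asks.

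**The concern.** The article justifies the sham arm as a way to separate the effect of iTBS from non-specific factors, and Objectives {7} expects some placebo response under sham. The sham removes such factors from the comparison only if they act equally in both arms. What a provider expects, and conveys through manner or remarks, is one of these factors. If the provider knows the arm, it can differ between arms.

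Keeping operators away from the ratings protects the rater from knowing the allocation. It does not protect the patient from cues received during treatment. A blinded rater records accurately whatever the patient has come to feel or report. BDI-II is self-reported and MADRS is a patient interview, so both can carry such an effect. They supply the antidepressant hypothesis in Objectives {7} and one side of the primary associations in Outcomes {12}.

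**Working it through.** No figure in the plan depends on this point: operator blinding does not enter the sample size of 46 (50 with drop-out). The check is a reading of the sections against each other.

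1. **Does the operator learn the arm?** {16b} puts a coil-type number in the envelope and {16c} has the operator open it. The key is given only as an example, and the article does not say outright that operators hold it. Two features point to an unblinded operator. Operators are absent from the blinded list in {17a}, and both {16c} and {17a} separate them from assessment, a precaution mainly needed for people who may know the arm. Unblinded is therefore the natural reading, though an inference.

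2. **Is there contact through which knowledge could act?** Yes. There are ten treatment days, with questions on well-being before and after each session. Whoever asks those questions, the operator is present to deliver the stimulation.

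3. **Does a stated safeguard close the route?** Role separation closes the route through the rater (detection bias). The article states no measure for the route through the patient (performance bias), such as a fixed script.

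4. **Which outcomes are exposed?**

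| Measure | How obtained | Exposure |
|---|---|---|
| BDI-II | Patient self-report | Direct |
| MADRS | Blinded clinician, patient interview | Through what the patient reports |
| N-back | Task performance | Less direct |
| Cortical thickness, FA, BOLD | Imaging | Less exposed |

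The associations join exposed and less exposed measures. If an association is computed across both arms, and imaging change also differs by arm, a provider-induced difference in depression scores would itself add to the association.

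5. **Can the route be narrowed with the equipment described?** {11a} says the coils match in look, weight and sound, so an operator could mount one by a neutral code. With only two codes, one disclosure reveals the key. {17a} discloses allocation to patients four weeks after the last stimulation, and Provisions for post-trial care {30} offers iTBS to eligible sham patients. Any code must therefore be renewable.

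6. **How large could the effect be?** The document gives no provider effect and no standard deviation of change, so no bias can be computed. As a yardstick only, the MADRS minimal clinically important difference of 13% in {12}, applied at the inclusion score of 20, is 0.13 × 20 = 2.6 points. A shift need not be many points to matter on that scale, but nothing in the document says that one will occur.

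**The case against.** The strongest reply is that this is a disclosed design choice. The article states exactly who is blinded, calls that double-blind, and keeps stimulating staff away from assessment. That stands: there is no internal contradiction and the label is not wrong as defined.

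Several stronger readings are tempting but unsupported:

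- **That operators are expressly told the allocation by one fixed key throughout.** The key is an example, and the article is silent on whether operators know it or whether it stays constant.
- **That one person gives a patient all ten sessions.** The article also speaks of staff members in the plural.
- **That the coils are indistinguishable to operators.** The claim covers look, weight and sound, and difficulty of separation is claimed only for naïve participants. The coils also act differently, so a trained operator might sometimes tell.
- **That the trial as a whole rests on subjective outcomes.** The primary outcome is cerebral change and its associations. Only MADRS and BDI-II depend on patient report.
- **That operators ask the session questions or decide on postponement and stopping.** {11b} names nobody. Nor does the article say whether the study nurses have seen the envelope. Silence in a condensed article is no fault.

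It is also fair that two-code masking is fragile once allocations are disclosed, and that recruitment has begun, so sessions already given cannot be re-blinded. These points limit the remedy. They do not remove the route for remaining participants.

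**Conclusion.** The concern holds as a design weakness in how the stated procedure is fixed. On the natural reading, operators know the arm during repeated contact over ten sessions, and the stated safeguard does not address what that knowledge may convey to the patient. BDI-II and MADRS, and the hypotheses and associations that use them, are exposed. Imaging measures are less so.

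The size is unknown. An inflated false-positive rate could be calculated by assuming a provider effect, but it would only restate that assumption. The conclusion rests on operators knowing the key. If they do not, the issue reduces to saying so in {16b} and {16c}. That the route is wholly avoidable is not established; that it can be narrowed at small cost is reasonable, given the coil description in {11a}.

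**What to change.** In {16b} and {16c}, have the envelope name a neutral coil code instead of a number indicating coil type. The key should be held only by the research assistant who prepares the envelopes and is not involved in data collection. That assistant should change the codes whenever a four-week disclosure or a post-trial active course could reveal the key.

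For remaining participants, and even if coding proves impracticable:

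- require operators to follow one fixed interaction script in both arms;
- state that they do not discuss allocation or expected benefit with patients;
- state in {17a} whether operators know the key and, if they do, report them as unblinded.

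The sponsor should also clarify who asks the session questions in {11b} and who makes postponement or stopping decisions, and whether those people know the allocation. No change to the clinical rules themselves is suggested.

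The cost is labels, a key list, periodic relabelling and a short script. Operators may still sometimes guess the coil, and sessions already delivered are unaffected. The script and the statement on operator blinding need only protocol wording and brief staff instruction, so they can be adopted while recruitment continues.

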## Assignment of interventions: blinding

### Who will be blinded {17a}

The patient will be blinded. The assessor of the patients’ clinical symptoms will be blinded. The staff members who provide iTBS will not assess the patient. Clinicians who assess the patients will not be aware of the treatment group. Thus, neither the clinician who assesses the patient nor the patient will know which treatment is provided. Four weeks after the last stimulation day, treatment allocation will be disclosed to the patient.

### Procedure for unblinding if needed {17b}

Serious adverse events will make unblinding permissible. A serious event will also stop the data collection until the reason for the event is clarified.

## Data collection and management

### Plans for assessment and collection of outcomes {18a}

At baseline, prior to stimulation, a clinical psychologist or a medical doctor will perform a diagnostic assessment using the M.I.N.I [24] and the MADRS [20] in a clinical interview. Information obtained from the participant at baseline includes age, sex, marital status, length of education, living situation, history of depression and comorbidity. The Maudsley Staging Method [31] is used to score the level of treatment resistance. A visual N-back task [32] is performed at a laptop and the BDI-II [21] is a self-report pen-and-paper measure.

The Maudsley Staging Method is a multidimensional model developed to define and stage treatment resistance in unipolar depression. The model maps treatment failures, severity of symptoms and duration of depressive episodes into a continuous score with a cut-off for treatment resistance [31].

The severity of depression symptoms will be evaluated using MADRS and the BDI-II. The MADRS will be administrated pre- and post-stimulation as well as once midway through the stimulation protocol and at close out. BDI-II will be administrated pre- and post-stimulation and again prior to close-out. At all-time points, the outcomes are collected by experienced clinical psychologists or a psychiatrist.

MADRS is a widely used clinician-administered instrument for measuring the severity of depressive episodes in patients with mood disorders. It consists of 10 items rated on a scale of 0 to 6, where higher scores indicate a higher degree of symptoms. MADRS has shown good concurrent validity [33, 34]. The MADRS has shown high correlations with other well-known and widely used clinician-rated scales such as the Hamilton Depression Rating Scale [35], underscoring the MADRS high concurrent validity. Intra-rater reliability was originally reported to be excellent [20]. However, subsequent studies have reported varying intraclass correlation coefficients (ICC). Maier et al. showed total scale score ICCs of 0.73, 0.66 and 0.82 in three separate samples [36]. It has later been demonstrated that the use of experienced clinicians as raters and the use of a structured guide for rating increases the intra-rater reliability. Williams and Kobak found an intraclass correlation for the total scale score between raters on the MADRS of 0.93 [37] whereas Geijer et al. [38] found an inter-rater reliability of ICC = 0.95.

The Beck Depression Inventory-II (BDI-II) [21] is one of the most widely used self-report instruments for assessing the severity of depression. It consists of 21 items and measures the degree of depression in ages 13 years and above. The concurrent validity of the BDI-II with other instruments and scales used to assess the severity of depression symptoms ranges from adequate to high with correlations ranging from 0.66 to 0.86 [39].

An n-back task [32] will be used to assess aspects of working memory, executive functions, reaction time and sustained attention to visual stimuli. The N-back is a widely used cognitive task that requires participants to concurrently encode, maintain, and update stimuli presented *n* trials previously [19]. The present study uses a visual in-house version of the task created in the software Psychopy [40] and presented on a laptop during the lab testing and on the MRI-scanner computer screen. In the present study, we will use 0-back and 2-back tasks. The instruction for the 0-back is to push the spacebar (for laptop administration) or the response button when in the fMRI lab as fast as possible when the letter “X” is presented on the screen. All other letters should be ignored. For the 2-back task, the participants should push the spacebar if the letter presented on the screen matched the letter presented two letters prior. Letters from A to Z are randomly presented with 1000 ms stimulus and 2000 ms interstimulus intervals in both the 0-back and the 2-back task. Participants are allowed to respond during the stimulus presentation and for 1000 ms after the stimuli ended. A total of 10 trials (five 0-back, and five 2-back) are performed in each run with a fixed order of the 0-back preceding the 2-back task. Participants will be tested 2 times (pre-test and post-test) outside the MRI scanner and two times (pre- and post-test) in the scanner. Hence, the order of the n-back runs are (1) pre-test in lab, (2) pre-test in MRI scanner, (3) post-test in lab, and (4) posttest in MRI-scanner.

### Plans to promote participant retention and complete follow-up {18b}

If a patient withdraws from the treatment, the information collected before the withdrawal will be kept and used. If a patient withdraws his or her study consent, the information collected will not be used.

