## Statistical methods

### Statistical methods for primary and secondary outcomes {20a}

Repeated measures data will be analysed by linear mixed models (LMM) which allow for a combination of fixed and random effects. LMM estimates the parameters using all available patient data and is thus less sensitive to scattered missing data, and has flexible modelling options for the covariance structure of the data [41]. Single means (e.g. baseline data) will be analysed with statistical methods within the framework of general linear models (GLM), if the statistical assumptions for GLMs are met. In case of non-normal data, non-parametric statistics will be performed. SPSS and R will be used for statistical analyses of clinical and cognitive data. Analyses of brain imaging data will be performed in separate programs according to the type of data. FreeSurfer (FS) (https://surfer.nmr.mgh.harvard.edu/) will be used for preprocessing of structural imaging data (volumetric analyses and segmentation), and Tracula inbuilt in FS will be used for DTI data [42], and Permutation Analysis of Linear Models (PALM) will be used to perform statistics on structural data preprocessed in FS, and in analyses where imaging data is combined with other data as covariates or factors [43]. SPM12 (https://www.fil.ion.ucl.ac.uk/spm/software/spm12/) will be used for preprocessing of fMRI data. An alpha value of 0.05 will be used for all analyses, and Bonferroni-corrections will be applied when appropriate for controlling the type-1 error rate.

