### Methods in analysis to handle protocol non-adherence and any statistical methods to handle missing data {20c}

Protocol non-adherence will be addressed using an intention-to-treat analysis, which includes all participants as originally allocated regardless of adherence. Missing data will not be imputed. Missing data will be reported in the manuscripts. Sensitivity analyses will be conducted to evaluate the impact of different missing data assumptions, such as missing not at random.

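### For imaging and N-back, the promised intention-to-treat analysis is in effect an analysis of patients who have both a pre-test and a post-test

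*Protocol article*

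**What the plan says.** All references are to the protocol article.

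- **Retention {18b}.** After treatment withdrawal: "If a patient withdraws from the treatment, the information collected before the withdrawal will be kept and used". After consent withdrawal: "If a patient withdraws his or her study consent, the information collected will not be used".
- **Non-adherence and missing data {20c}.** The plan promises "an intention-to-treat analysis, which includes all participants as originally allocated regardless of adherence", and adds "Missing data will not be imputed". It also says: "Sensitivity analyses will be conducted to evaluate the impact of different missing data assumptions, such as missing not at random".
- **Outcomes {12}.** The primary outcome is cerebral change and its association with change in symptoms and N-back performance. Imaging takes place once before and once after the stimulation course.
- **Assessment plans {18a}.** N-back has one pre-test and one post-test on the laptop, and the same in the scanner. MADRS is also rated midway and at close-out. BDI-II is repeated before close-out.
- **Discontinuation criteria {11b}.** These are "worsening of disease, report of adverse side effects, withdrawal of consent, change in drugs or not receiving stimulation on more than 2 days". No data rule is attached to patients discontinued on these grounds.
- **Statistical methods {20a}.** Repeated measures go to linear mixed models on all available data. For structural imaging, "Permutation Analysis of Linear Models (PALM) will be used to perform statistics on structural data preprocessed in FS".
- **Sample size {14}.** The fMRI analysis needs 46. A drop-out rate taken from rTMS treatment (7 to 8%, set at 10%) raises enrolment to 50.

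**The concern.** Read together, these rules do not deliver what {20c} promises. A patient who stops before the second scan, and whose usable data end at that point, has a baseline scan and nothing to compare it with. Without imputation, that patient has no value on the primary imaging outcome. The same holds for N-back, which has only one post-test in each setting.

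The loss may be informative. Several of the {11b} criteria, such as worsening, side effects and drug change, are plausibly linked to how the patient is doing, and side effects could differ between active and sham stimulation. If so, the comparison of patients with both scans no longer has the protection of randomization, while the report would still carry an intention-to-treat label. A post-test that was not obtained cannot be recovered later.

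**Working it through.** **1. The plan's own figure.** Inputs from {14}: f = 0.25, two groups, alpha 0.05, power 0.90, correlation 0.5, sphericity 1. Two measurements follow from {12}. For the group-by-time interaction, λ = f² × N × m / (1 − ρ) with df = (1, N − 2). At N = 46, λ = 0.0625 × 46 × 2 / 0.5 = 11.5 and power is 0.9125; N = 44 gives 0.8997. So 46 is reproduced. With 50 enrolled and 10% lost, 50 × 0.9 = 45 remain and power is 0.906. Lost power is not the problem.

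**2. The planned effect in SDs of change.** A two-group comparison of change scores has λ = d² × N / 4. Setting d² × 46 / 4 = 11.5 gives d = 1.0. Shifts in SDs of change should be judged against 1.0.

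**3. Whether the mixed model rescues baseline-only patients.** Simulation with 50 patients, two time points, correlation 0.5, and 5 post-test values missing completely at random (150 runs): the interaction SE is 0.294 with the baseline-only patients and 0.298 without them, and the two estimates correlate at 0.98. These patients add almost nothing to the change contrast, so the choice between LMM and PALM hardly matters here.

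**4. Size of a possible shift in the between-arm contrast.** All stopping patterns below are assumptions; none is in the document.

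| Assumption | Calculation | Shift (SD of change) |
|---|---|---|
| Worst 10% of one arm on the outcome leave, none from the other | φ(z₀.₁₀) / 0.90 | 0.195 |
| 10% leave one arm only; reason for stopping correlates 0.5 with the imaging outcome | 0.5 × 0.195 | 0.10 |
| As above, correlation 0.3 | 0.3 × 0.195 | 0.06 |
| Stoppers 1 SD worse, 16% vs 4% stop | 1 × (0.16 − 0.04) | 0.12 |
| Stoppers equally worse in both arms, 10% vs 10% stop | 1 × (0.10 − 0.10) | 0 |

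The first row is 0.195 / 1.0, about 20% of the planned effect. With no true effect and 45 analysed, the 16% vs 4% row raises the type I error from 0.05 to about 0.068.

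**5. Equal stopping, unequal deficits.** Suppose 10% stop, stoppers in the active arm keep none of the effect, and f = 0.25 holds among the rest. The as-allocated effect is 0.25 × 0.9 = 0.225, so the both-scans analysis overstates it by 1/0.9 − 1 = 11%. If stoppers keep half the effect, the overstatement is 1/0.95 − 1 = 5%. If they keep all of it, there is none.

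**The case against.** The strongest reply is that {18b} is a rule about retaining data. It contrasts treatment withdrawal, where earlier data are kept, with consent withdrawal, where they are not. It does not forbid a later scan, and the article condenses a fuller protocol that is not shown. This stands in part: a reader might infer that post-tests after stopping are ruled out, and the text does not say so. But no section provides for one, and {14} uses a treatment drop-out rate to go from 46 to 50, which treats those who stop as lost to the fMRI analysis.

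The second reply is that {18b} speaks of patients who withdraw, whereas {11b} also covers patients who are discontinued. This is correct. The article states no data rule for the latter, so it cannot be said that they lose their post-test by rule.

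Three stronger readings are not supported:

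- **A shift of 40% of the effect.** A reader might convert f = 0.25 to d = 0.5 and obtain 0.20 / 0.5. The document does not state d = 0.5, and under its own inputs the interaction corresponds to d of about 1.0 on change.
- **The no-imputation rule contradicts the missing-not-at-random analysis.** It does not. Selection and pattern-mixture models can be fitted by likelihood without imputation, and the choice of method can be left to an analysis plan.
- **Replacing PALM by mixed models on regional summaries would restore intention-to-treat.** Step 3 shows that it would recover almost nothing.

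The planned sensitivity analyses soften the problem, but they supply no data after stopping and leave the main analysis unchanged.

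**Conclusion.** The point holds in limited form. As written, the plan yields an analysis of patients with both scans under an intention-to-treat label for the primary imaging outcomes, and likewise for N-back. This rests on the absence of any provision for a post-test after stopping and on the sample size reasoning, not on an express prohibition.

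MADRS is less affected because its midway rating can enter the mixed model. BDI-II is less affected to the extent that its close-out value is obtained.

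Bias in the between-arm contrast needs stopping, or the relation of stopping to outcome, to differ by arm. Under the assumptions shown, it ranges from none to about 0.12 SD of change, with 0.20 SD (about 20% of the planned effect) in a one-sided worst case. This is modest at the planned 10% drop-out, but it affects the primary outcome and is cheap to reduce.

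**What to change.** Amend {18b} to say that patients who stop stimulation for any reason, whether they withdraw from treatment or are discontinued under {11b}, and who still consent, are invited to the scheduled post-test (MADRS, BDI-II, N-back, MRI) and to close-out, and that these data are analysed as allocated. In {20c}, state that where a second scan is still missing, the imaging analysis set is patients with both scans, and do not call it intention-to-treat. Patients who withdraw consent remain outside the analysis under {18b}; {20c} should acknowledge that exception. PALM and the no-imputation rule can stay.

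The cost is a short amendment and attendance by about five of 50 patients (10%) at visits already scheduled. Including them may dilute the effect. If stoppers in the active arm keep none of it, power with all 50 analysed is 0.877, against 0.906 for 45 patients with both scans; if they keep half, it is 0.908.
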